## Discussion

Alzheimer’s disease has become one of the most serious health concerns, due to increasing life span and aging populations worldwide. The disease is a chronic, progressive neurodegenerative disorder, characterized by pathological changes including neuritic plaques and neurofibrillary tangles, which accumulate years before clinical symptoms manifest [15]. Early treatment of MCI patients could halt or slow down irreversible progression of neurodegeneration to AD [16]. Nevertheless, there is no proven treatment for MCI to date [17]. In this trial, we will explore the potential of KGT as a therapeutic agent for MCI patients.

Clinical symptoms are not evident in MCI, so we will utilize an extensive assessment to evaluate the effect of KGT on cognitive function and disease progression. Instruments, such as the K-MMSE and the Alzheimer’s Disease Assessment Scale-cognitive subscale (ADAS-cog), have been mainly used in previous studies for measuring cognitive decline. However, they lack sensitivity in detecting mild degrees of cognitive dysfunction, which demonstrate ceiling effects in MCI [18]. We will use the full neuropsychological battery, the SNSB, which contains comprehensive and diverse tests with varying difficulties, to sensitively and accurately monitor changes in cognitive function [11].

We will also measure neuroimaging markers that reflect dynamic neuropathological processes. Structural MRI-based measurements of brain atrophy are the most widely accepted marker of AD progression [19]. However, the utility of structural MRI for MCI is limited because overt loss of neurons and associated brain atrophy occur in the later stages of AD [20]. Functional changes also occur in the brains of MCI and AD patients. There is consistent reduction of cerebral metabolism, blood flow, and disturbances in neurotransmission that precede substantial brain atrophy [21]. Therefore, changes in brain metabolite and neurotransmitter levels, and cerebral blood flow will be measured in this trial.

Proton MRS is a sensitive method for estimating brain metabolite and neurotransmitter concentrations [22], including NAA, myo-Inositol (mI), choline (Cho), Glx, and GABA, frequently measured as ratios to creatine [23]. A decrease in concentrations of NAA, a neuronal metabolite, and Glx, a component of the excitatory neurotransmitter system in the brain, is indicative of neuronal dysfunction in AD [24]. Detecting changes in neuronal markers may be suitable for assessing treatment responses.

Arterial spin-labeling perfusion MRI (ASL MRI) is used to quantify regional cerebral blood flow (rCBF) [25]. Alzheimer’s disease patients show regional hypoperfusion that reflects patterns of reduced brain functional activity, using this technique [26]. Studies have suggested that ASL MRI is appropriate for examining neural response to pharmacological agents [27]. Prior studies that measured rCBF used Single Photon Emission Computed Tomography (SPECT). However, ASL MRI is advantageous because there is no exposure to ionizing radiation or the need for intravenously administered contrast agents, and there is higher accessibility, lower cost, and higher spatial resolution [26].

As secondary outcomes, we will observe changes in blood-based biomarkers levels, including Aβ protein, tau protein, HMGB, SERF 1A, and cholesterol derivatives, which are proposed to be associated with AD pathology [28]. Aβ protein and tau proteins are the main feature of AD neuropathology, and are closely associated with neuronal loss. High plasma Aβ levels are a risk factor for AD [29]. High total cholesterol levels accelerate the production of Aβ protein in AD, and are related to increased cognitive impairment in humans [30]. The strongest genetic risk factor for AD, *APOE* genotype, will also be determined by plasma *APOE* proteins [31]. This genetic marker will provide information for distinguishing which patients are most likely to benefit from KGT administration.

This pilot study will be the first rigorous clinical analysis of KGT for the treatment of aMCI, and should provide evidence for the effectiveness and safety and of KGT. Our extensive assessment, using various biomarkers, should reveal the mechanisms underlying the effect of KGT on disease progression. The findings will support a large-scale confirmatory clinical trial to gather evidence for KGT use in MCI patients.

There are some limitations in this protocol. The target sample size is relatively small, and the sample size could not be calculated by standard methods. However, this is a pilot study to generate data for sample size calculations in a future randomized trial, which will include a larger sample size. Also, the total intervention period is 24 weeks and the monitoring period after the completion of taking medicine is 4 weeks, which is relatively short considering the nature of the disease. Long-term follow-up will be necessary in future trials.

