### Outcome

Primary outcomes will include changes in cognitive function, and changes in imaging biomarkers, before and after taking KGT or placebo granules. For assessing cognitive function, the SNSB will be conducted and changes in SNSB results will be analyzed. For measuring the imaging biomarkers, brain MRI scans will be taken to assess the levels of brain metabolites, neurotransmitters, and cerebral blood flow (CBF).

Secondary outcomes will include the safety of KGT granules, and changes in blood-based biomarkers including proteins (amyloid β (Aβ) and tau) and cholesterols, and a comparison of MRI changes between the two groups using age and genotype as covariates. For safety assessments, blood chemistry tests for AST/ALT, glucose, blood urea nitrogen (BUN), Cr, Na, K, Cl, lactate dehydrogenase (LDH), creatine phosphokinase (CPK), and an electrocardiogram (ECG) will be conducted. Blood biomarkers including Aβ protein, tau protein, high-mobility group box (HMGB), small EDRK-rich factor (SERF) 1A, and cholesterol derivatives will also be measured. *APOE* genotype testing will be performed. Detailed explanations are shown below.

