### Assessments

#### K-MMSE and SNSB

The K-MMSE will be performed at the screening visit and after 12 weeks of medication, to screen for MCI and assess the cognitive status of participants. This is a simple screening test for the longitudinal assessment of general cognition [10].

The full version of the SNSB-II will be measured at baseline and after 24 weeks of medication, to evaluate the effect of *Kami Guibi-tang* on cognitive function. The change in the mean of the SNSB scores, including the SNSB for dementia (SNSB-D) scores, will be compared between the KGT and placebo groups as a primary outcome.

The SNSB is one of the standardized neuropsychological test batteries, widely used in South Korea, for assessing general cognitive abilities. The test is composed of multiple subtests, which evaluate five cognitive aspects: attention, memory, language, visuospatial function, and executive function. Other related tests are included, such as the K-MMSE, Clinical Dementia Rating (CDR), Barthel–Activities of Daily Living (BADL), and Geriatric Depression Scale (GDS). The estimated completion time of the whole battery is 1.5–2 h [11].

A modified version of the original SNSB for dementia (SNSB-D) will be used to provide a general cognitive functioning (GCF) score, drawn from the sum of five domains. The maximum total score is 300 points consisting of 17/300 (6%) for attention, 27/300 (9%) for language and related function, 36/300 (12%) for visuospatial function, 150/300 (50%) for memory, and 70/300 (23%) for frontal/executive function [12]. The contents of the SNSB-D are shown in Table 2.

**Table 2 Tab2:** Contents of the Seoul Neuropsychological Battery for Dementia (SNSB-D)

Domains (total score)	Subtests	Maximum points
Attention (17)	Digit span forward	9
	Digit span backward	8
Language and related function (27)	K-BNT	15
	Calculation	12
Visuospatial function (36)	RCFT copy	36
Memory (150)	Orientation	6
	SVLT free/delayed recall	48
	SVLT recognition	12
	RCFT free/delayed recall	72
	RCFT recognition	12
Frontal/executive function (70)	Motor impersistence	3
	Contrasting program	3
	Go-no-go test	3
	Fist-edge-palm	3
	Luria loop	3
	Categoric word generation	20
	Phonemic word generation	15
	Stroop test-color reading	20
GCF score		300

*K-BNT* Korean short version of the Boston Naming Test, *RCFT* Rey Complex Figure Test, *SVLT* Seoul Verbal Learning Test, *GCF* global cognitive function

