#### MRI

Participants will undergo brain MRI at baseline and after 24 weeks of medication, to measure changes in brain metabolite and neurotransmitter levels, cerebral blood flow, tissue volume, and to evaluate brain abnormalities.

Proton magnetic resonance spectroscopy (^1^H-MRS) will be used to measure brain metabolite and neurotransmitter levels. Single-voxel Point-RESolved Spectroscopy (PRESS) MRS will be performed at the precuneus and posterior cingulate area of the brain, with a voxel size of 30 mm × 30 mm × 30 mm, to detect *N*-acetylaspartate (NAA) and glutamate-glutamine complex (Glx, with both Glu and Gln). *N*-acetylaspartate and Glx will be quantified using LCModel software. MEshcher-GArwood (MEGA) PRESS MRS will be performed to detect gamma-aminobutyric acid (GABA) in the same area as the PRESS MRS. The amount of GABA will be quantified using GANNET software. Pseudo-continuous arterial spin-labeling (pCASL) MRI will be performed to measure cerebral blood flow (CBF) in the brain. Voxel-based CBF will be mapped using local software. A three-dimensional T1-weighted image will be acquired using the magnetization-prepared rapid gradient-echo (MPRAGE) sequence, to quantify the gray and white matter tissue volume in the brain. T2-weighted turbo-spin echo (TSE), and fluid attenuation inversion recovery (FLAIR) sequences, will be used to evaluate brain abnormalities in participants. Changes in CBF and mean levels of NAA/Cr, Glx/Cr, and GABA/Cr, will be compared between KGT and placebo groups, as a primary outcome.

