#### Genotyping

Apolipoprotein E (*APOE*) epsilon genotyping (e23, e33, e34, e44) will be performed using blood samples at baseline, to determine if the effect of KGT is influenced by *APOE* genotype. The changes in mean values of NAA/Cr, Glx/Cr, GABA/Cr, and CBF before and after the intervention will be compared between carriers and non-carriers of the *APOE* epsilon 4 allele.

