#### Data analyses

The investigators, along with an independent professional statistician, will perform the data analyses. All statistical analyses will be performed using SPSS for Windows. The effectiveness test will be performed using the intention-to-treat (ITT) principle and the per-protocol (PP) principle. Missing data will be adjusted with the last-observation-carried-forward (LOCF) imputation method. The safety test will be analyzed using the ITT principle, without adjustment. We will not perform interim analysis.

The student’s *t* test will be used for parametric variable comparisons between the two groups, and the paired *t* test will be used for intra-group comparisons. The Mann-Whitney *U* test will be used for non-parametric variable comparisons between the two groups, and the Wilcoxon signed-rank test will be used for intra-group comparisons.

The paired *t* test will be used to compare changes in MRI measurements, blood proteins, and cholesterol levels, before and after treatment. Correlation analysis will be used to estimate the relationship between the changes in MRI measures and changes in blood test results. Linear regression analysis will be used to compare changes in MRI measures, between the study group and the placebo group, using age and *APOE* genotype as covariates. Statistical significance will be set at *P* < 0.05, and all tests will be two-tailed.

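### The plan says APOE will help identify who benefits from KGT, but both genotype analyses are limited to MRI measures and neither names a treatment-by-genotype contrast

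*Protocol article*

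**What the plan says.** In the Discussion, the article says of APOE genotype: "This genetic marker will provide information for distinguishing which patients are most likely to benefit from KGT administration". The Genotyping section gives the purpose of the test as "to determine if the effect of KGT is influenced by" APOE genotype, and then names the analysis: "The changes in mean values of NAA/Cr, Glx/Cr, GABA/Cr, and CBF before and after the intervention will be compared between carriers and non-carriers" of the e4 allele.

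The Outcome section lists, as a secondary outcome, "a comparison of MRI changes between the two groups using age and genotype as covariates". Data analyses repeats this: "Linear regression analysis will be used to compare changes in MRI measures, between the study group and the placebo group", with age and APOE genotype as covariates.

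For cognition, the K-MMSE and SNSB section says that the change in SNSB scores, including the SNSB-D, "will be compared between the KGT and placebo groups as a primary outcome". Genotype is not mentioned there. The MRI section makes imaging a primary outcome as well: "Changes in CBF and mean levels of NAA/Cr, Glx/Cr, and GABA/Cr, will be compared between KGT and placebo groups, as a primary outcome".

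**The concern.** The question of which patients benefit from KGT needs two things: an outcome that represents the benefit, and a contrast that shows whether the KGT-placebo difference varies with genotype. The article names the endpoints of its genotype analyses, and the cognitive primary outcome is not among them. It also names the form of those analyses, and neither form is a treatment-by-genotype contrast.

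At stake is how the pilot will be read. The article presents it as groundwork for a large confirmatory trial. A carrier versus non-carrier difference in NAA/Cr or CBF could be reported under the Discussion sentence as showing who benefits. It would have no cognitive counterpart, and it might reflect how carriers change regardless of treatment.

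**Working it through.** **1. Endpoints and form of each analysis that uses genotype, with the SNSB analysis for comparison**

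| Analysis | Section | Outcome | Contrast |
|---|---|---|---|
| Carrier comparison | Genotyping | NAA/Cr, Glx/Cr, GABA/Cr, CBF | e4 carriers vs non-carriers |
| Adjusted regression | Outcome; Data analyses; also Abstract | MRI changes | KGT vs placebo, with age and APOE as covariates |
| SNSB comparison | K-MMSE and SNSB | SNSB, SNSB-D | KGT vs placebo, no genotype |

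Analyses that use genotype: 2. With a cognitive endpoint: 0. With a treatment-by-genotype term: 0.

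**2. What the named contrasts estimate**

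Write the mean change in each cell as follows:
- placebo, non-carrier: a
- placebo, carrier: a + g
- KGT, non-carrier: a + t
- KGT, carrier: a + g + t + m

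Here g is the difference between carriers and non-carriers without KGT, t is the KGT effect in non-carriers, and m is the amount by which the KGT effect differs in carriers. The stated aim is about m. With equal arms and the same carrier share f in both:
- Carriers minus non-carriers, arms pooled: g + m/2.
- Carriers minus non-carriers, KGT arm only: g + m.
- Regression with APOE as a covariate and no interaction: treatment coefficient t + f·m, genotype coefficient g + m/2.

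None of these isolates m. Only the difference of differences does: (KGT − placebo in carriers) − (KGT − placebo in non-carriers) = (t + m) − t = m. Adding the SNSB to the two analyses in their present form would therefore not answer the question either.

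**3. Precision of the missing estimate**

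The plan's own figure reproduces: 30/(1 − 0.20) = 37.5, rounded up to 38 (Sample size calculation). With 1:1 allocation, 30 evaluable participants are 15 per arm. The article gives no carrier share. I assume f = 0.3 to 0.5, the same in both arms, and a common SD of the change.

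SE(m) = SD × sqrt(2/(15f) + 2/(15(1 − f))). With four cell means there are 30 − 4 = 26 degrees of freedom, and the t quantile is 2.056.

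| f | Carriers / non-carriers per arm | SE(m), SD units | 95% CI half-width, SD units |
|---|---|---|---|
| 0.3 | 4.5 / 10.5 | 0.80 | 1.64 |
| 0.4 | 6.0 / 9.0 | 0.75 | 1.53 |
| 0.5 | 7.5 / 7.5 | 0.73 | 1.50 |

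For comparison, the SE of the overall KGT effect is sqrt(2/15) = 0.37 SD, so the interaction SE is at least twice as large (0.73/0.37). If all 38 were analysed (19 per arm), SE(m) would be 0.71 to 0.65 SD, which is still imprecise.

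**The case against.** The best reply is that imaging is itself a declared primary outcome. The Background lists the influence on imaging and neurochemical biomarkers among the aims, and the Discussion explains why functional imaging was chosen for MCI. A genotype analysis of NAA/Cr, Glx/Cr, GABA/Cr and CBF therefore uses primary endpoints. This stands. A reader might infer that an MRI result by genotype says nothing about treatment response; the documents do not support that. The limit is narrower: such a result concerns imaging response, not cognitive benefit.

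The Discussion sentence is also mild. It says the marker will provide information, not that it will settle who benefits. It governs no analysis, the trial calls itself a pilot, and small size is listed as a limitation. This too stands, and it keeps the point modest. But the same aim appears in the Genotyping section, where it introduces an analysis.

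A third reply is that an article condenses the full plan. That would excuse silence. Here the article names the endpoints and the form of both genotype analyses, so the mismatch lies in what it states.

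A reader might also fault the plan for never relating MRI change to cognitive change, since the only correlation named is this: "Correlation analysis will be used to estimate the relationship between the changes in MRI measures and changes in blood test results". The article nowhere claims that the MRI measures will be validated against cognition, and such associations are commonly left to the full plan. Their absence is no error. Nor does the wide interaction CI prove the mismatch: it reflects sample size and applies equally to MRI and SNSB endpoints.

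**Conclusion.** The point holds in a limited form. The aim of learning whether APOE influences the effect of KGT, and the Discussion statement about who is likely to benefit, go further than the genotype analyses described. Those analyses have MRI outcomes only, and neither names the treatment-by-genotype contrast that the aim requires. This conclusion rests on the text alone and on no assumed figure.

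The consequence is confined to secondary and exploratory results and their interpretation; the KGT-placebo comparisons of SNSB and MRI do not depend on it. It is worth correcting because the remedy uses data already planned. The half-width of about 1.5-1.6 SD indicates how cautiously any result should be worded. It depends on 15 analysed per arm, 30-50% carriers, equal carrier shares in the arms and a common SD.

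**What to change.** 1. **Data analyses:** add the change in the SNSB-D GCF score as an outcome of the age- and APOE-adjusted regression.
2. **Data analyses and Genotyping:** add an exploratory treatment-by-e4-carrier term for GCF change and for each of the four MRI measures: change = b0 + b1·KGT + b2·e4 + b3·age + b4·(KGT × e4). Report b4 as an estimate with its 95% CI, labelled exploratory. Including age leaves 25 degrees of freedom and does not change the half-widths above to one decimal.
3. **Discussion:** reword the APOE sentence to say that the trial will give only an exploratory, imprecise estimate of the KGT effect by e4 status.
4. **Optional:** associations of GCF change with MRI change, also labelled exploratory.

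SNSB and MRI are both measured at baseline and 24 weeks, and APOE at baseline, so no visit, sample or procedure is added. The terms should be fixed before unblinding. The cost is a few more model runs and a few more imprecise results to label as exploratory. If the sponsor wants no new analysis, the minimum is to limit both the Discussion sentence and the Genotyping aim to an exploratory description of imaging change by genotype.

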## Trial status

This study began recruitment in May 2017 and we have currently enrolled 33 participants.

## Data Availability

Not applicable.

## Abbreviations

AD: Alzheimer’s disease
ADAS-cog: Alzheimer’s Disease Assessment Scale-cognitive subscale
ALT: Alanine aminotransferase
aMCI: Amnestic mild cognitive impairment
ASL MRI: Arterial spin-labeling perfusion magnetic resonance imaging
AST: Aspartate aminotransferase
BUN: Blood urea nitrogen
CBF: Cerebral blood flow
CDR: Clinical Dementia Rating
GDS: Global Deterioration Scale
KDSQ: Korean Dementia Screening Questionnaire
KGT: *Kami Guibi-tang*
K-MMSE: Korean Version of Mini-Mental State Examination
MCI: Mild cognitive impairment
MRS: Magnetic resonance spectroscopy
NINCDS-ADRDA: National Institute of Neurological and Communicative Disorders and Stroke and Alzheimer’s Disease and Related Disorders Association
pCASL MRI: Pseudo-continuous arterial spin-labeling perfusion magnetic resonance imaging
rCBF: Regional cerebral blood flow
SNSB: Seoul Neuropsychological Screening Battery
